## Methods

### Study design

An overview of the study design appears in Fig. 1. We are conducting a 2-arm RCT using a wait-list control. We will recruit 250 adult Native Hawaiians with confirmed HTN and perform a 1:1 randomization within each study site, such that 125 are assigned to the intervention and 125 are assigned to the wait-list control arm. The hula intervention will be delivered by experienced *kumu hula* and trained community peer educators to groups of 12 to 15 at each study site following standardized protocols. Our primary outcomes are reductions in SBP and improvements in CVD risk as measured by the Framingham Risk Score (FRS). We elected to focus on SBP instead of DBP because the former is a stronger predictor of CVD risk, and its predictive strength increases with age [47–49]. Changes in SBP and FRS from baseline will be compared between study arms at 3-month and 6-month follow-ups. Wait-list participants will be offered the hula intervention after completing their 6-month follow-up. The original intervention arm will also complete a 12-month follow-up to assess the maintenance of SBP and FRS improvements.

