#### Intervention arm

Participants randomized to the intervention will begin the 6-month *Ola Hou* program within 1 week of completing the HTN self-management course. The first 3 months of the intervention were designed and standardized as a culturally-based program of physical activity involving 12 weeks of hula training. Training will be delivered in the form of two 60-min classes per week over 12 weeks (24 classes total). Each class will include about 10 to 20 participants, and will offer opportunities for social engagement and support. The hula class format in this study was previously evaluated and found to offer an appropriate level of physical activity in accordance with national recommendations [21], including recommendations for people with limited mobility and fitness [41]. Lessons are led by a *kumu hula* trained in the standardized protocols developed by the study’s lead *kumu hula*. Each 60-min lesson aims to increase the amount of time engaged in continuous dancing, from 5 to 10 min in week 1 to 40 min by week 12. BP devices will be given to participants to help them regularly self-monitor BP throughout the study period. Table 1 outlines the phases, activities, and goals of each lesson.

**Table 1 Tab1:** Summary of each 60-min hula lesson in the *Ola Hou* program

Phase	Duration	Activities and goals
Warm-up	5–15 min	Stretching legs, arms, and lower back Low-level hula activity at 25–40% MPHR
Conditioning	20–40 min	Moderate-intensity hula 40–85% VO_max_ or 50–70% MPHR Training intensity = (40 + [2 x Max MET]) % RPE = Between 12 and 16 on Borg scale^a^ Target HR = (HR reserve x training intensity [%]) + HR_resting_
Cool-down	3–10 min	Low-level hula to return HR and blood pressure to resting level

*Abbreviations: MPHR* maximum predicted heart rate, *VO*
_*max*_ maximal oxygen consumption, *MET* metabolic equivalent, *RPE* rating of preceived exertion, *HR* heart rate

^a^The Borg scale is a subjective measure of physical exertion. Scores range from 0 to 20

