#### Statistical analysis

For our first two research aims, statistical analyses will be done on an intention-to-treat basis, with differences between study arms in mean changes in SBP and FRS as the primary outcomes. Participant characteristics and rates of recruitment, retention, and intervention fidelity will be summarized by using descriptive statistics. To test the hypothesis that the intervention will lead to significantly more reduction in SBP and FRS relative to the control condition, mean changes in SBP and FRS between baseline and 3-month and 6-month follow-up will be analyzed by independent t-tests between the 2 arms. Analysis of covariance and general linear modeling approaches will then be used to adjust for relevant covariates, such as gender, age, type of community, and baseline SBP and FRS values. Missing values for SBP and FRS at follow-up visits will be imputed by carrying forward baseline observations. If a covariate value is missing, it will be assumed to be missing at random. For sensitivity analyses, mean changes in SBP and FRS of participants who complete follow-up data collection will be analyzed by using a complete case analysis method. A stratified analysis will also be conducted within site or by gender to explore the potential impact of such factors on outcomes. In addition, data collected at all study visits will be modeled by repeated measures analysis of variance and linear mixed effects models, incorporating correlated data from multiple visits, to examine the post-intervention maintenance of SBP and FRS improvements. Determination of the appropriate covariance matrix in the repeated measure analysis will be based on quality of fit to the data by using the method of Fitzmaurice et al. [73]. Statistical analyses will be performed in SAS 9.4 (2015 SAS Institute Inc.). A two-tailed *p*-value <0.05 will be regarded as statistically significant.

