#### Power analysis and sample size

Our proposed target of 250 enrolled participants (125 per arm) is based on an anticipated attrition rate of 20%. To test the efficacy of the intervention, our sample size calculation was based on mean differences in SBP in our pilot study [42], which demonstrated a 3-month mean change in SBP of 7.5 mmHg (SD = 16.5) between 2 arms randomized 1:1. Assuming that 206 participants (103 per arm) complete all follow-up assessments, we will have 90% statistical power to detect a similar effect size in our ongoing study.

Although we plan to compare CVD scores between the tow study arms, no FRS data specific to the Native Hawaiian population are available. Therefore, we used data from a previous community-based intervention to calculate the necessary sample size. In a 1-year study with a multiethnic sample recruited in medically underserved urban and rural communities (*n* = 195; 59% White, 37% Black, and 4% Hispanic), the biggest changes in FRS were observed at month four [59]. The reported average reduction in FRS varied according to differences in initial risk profiles – for example, 6.0% (SD = 9.9%) for participants at high risk (FRS ≥ 20) and 1.3% (SD = 4.5%) for participants at intermediate risk (20 > FRS ≥ 10). Among study participants, 63% had HTN, with baseline averages of SBP = 146 mmHg and DBP = 82 mmHg, almost identical to the baseline averages in our pilot study (SBP = 146 mmHg, DBP = 86 mmHg). Given a similar mean change in FRS for participants at intermediate risk, a sample of *n* = 206 will provide 80% statistical power to detect a change in FRS of 1.3% (SD = 4.5%) at 6-month follow-up.

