Another innovation of this study is our analysis of psychosocial and sociocultural constructs (e.g., cultural identity, perceived ethnic discrimination) that might mediate the intervention effect on BP control. Our pilot study found that the intervention reduced perceptions of racism, and preliminary findings of other ongoing studies indicate that Native Hawaiian ethnic identity is positively related to behavioral and emotional self-control. Thus, our design responds to a transdisciplinary call for studies of the mechanisms underlying behavioral interventions [80–82].

Our ongoing study also has limitations. First, implementing the intervention at several different sites makes it difficult to ensure the consistency in delivery required by standardization, and might therefore introduce confounders into our analyses. To minimize this possibility, we will conduct fidelity checks and offer booster training sessions as needed. Second, we rely on self-report measures for many variables of interest, potentially introducing biases involving recall and social desirability. Nevertheless, self-report is the primary method of assessing attitudes, beliefs, and other cognitive processes, and we will use measures validated in previous studies with Native Hawaiians to minimize self-reporting biases. Third, we anticipate that more women than men might participate, since dancing might be more attractive to women. Accordingly, we will make special efforts to recruit Native Hawaiian men to achieve balanced gender representation.

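### Only the intervention arm is taught in shared hula classes, yet the primary t-test and the 90% power assume independent participants; if outcomes correlate within class, the test is somewhat liberal and the power optimistic

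*Protocol article*

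**What the plan says.** The Randomization section allocates individuals 1:1 within site, in cohorts of 20 to 40, with half of each cohort going to each arm.

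The intervention arm is then taught together. Under Intervention arm: "Each class will include about 10 to 20 participants, and will offer opportunities for social engagement and support". The Study design section has the intervention delivered to "groups of 12 to 15 at each study site following standardized protocols". There are 24 lessons over 12 weeks. In months 4 to 6 there are weekly group meetings with a peer educator and a monthly hula lesson. Controls have no hula classes until their 6-month visit. The hypertension course goes to both arms, so it does not create clustering in one arm only.

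In the Statistical analysis section, changes in SBP and FRS "will be analyzed by independent t-tests between the 2 arms". Adjusted models follow, with gender, age, type of community and baseline values as example covariates. The mixed models are there for correlation across visits within a person. Site appears in an exploratory stratified analysis. No class, cohort or instructor term is named.

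The Power analysis section takes the pilot effect, "which demonstrated a 3-month mean change in SBP of 7.5 mmHg (SD = 16.5) between 2 arms randomized 1:1", and concludes: "Assuming that 206 participants (103 per arm) complete all follow-up assessments, we will have 90% statistical power to detect a similar effect size". It gives no ICC or design effect.

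The Discussion accepts that using several sites "makes it difficult to ensure the consistency in delivery required by standardization", and answers with fidelity checks and booster training.

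**The concern.** People in the same class share a teacher, a schedule, a room and one another. Social support is a stated feature of the classes and a measured candidate mediator, so some resemblance in outcomes within a class is plausible, and it would arise in one arm only. An independent t-test gives no weight to that shared component. When the component is present, the variance of the intervention mean is larger than the test assumes, the nominal 5% is exceeded, and the planned sample buys less power than stated.

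The trial is presented as a more definitive follow-up to a pilot. A borderline result from this t-test could fairly be challenged on this ground. The point concerns a test and a power figure that the protocol states, not detail left to an analysis plan.

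**Working it through.** **Inputs.** Difference 7.5 mmHg, SD 16.5, 103 completers per arm (Power analysis). For the significance level: "A two-tailed *p*-value <0.05 will be regarded as statistically significant". Class size 10 to 20 (Intervention arm). Enrolled per arm: 125 (Study design). The ICC is not given; 0.01, 0.02 and 0.05 are assumed.

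**Step 1: the plan's own figure.** SE = 16.5 × √(2/103) = 2.299. Power = Φ(7.5/2.299 − 1.96) = Φ(1.302) = 90.4%; the noncentral t gives 90.1%. The stated 90% reproduces, with a design effect of exactly 1.

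**Step 2: how many classes.** Class size refers to classes as formed, so the count comes from enrolment: 125/20 = 6.25 and 125/10 = 12.5, or about 6 to 12 classes. Groups of 12 to 15 give 125/15 = 8.3 to 125/12 = 10.4, inside that range. Dropout shrinks classes without removing them, so completers per class are m = 103/12 = 8.58 to 103/6 = 17.17.

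**Step 3: design effect in one arm.**
- DE = 1 + (m − 1) × ICC
- SE = 16.5 × √((DE + 1)/103)
- Power = Φ(7.5/SE − 1.96)
- t-test type I error = 2 × (1 − Φ(1.96 × 2.299/SE))

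| Classes | ICC | DE | SE | Power | Type I error |
|---|---|---|---|---|---|
| 12 | 0.01 | 1.076 | 2.342 | 89.3% | 5.4% |
| 12 | 0.02 | 1.152 | 2.385 | 88.2% | 5.9% |
| 12 | 0.05 | 1.379 | 2.508 | 84.9% | 7.2% |
| 6 | 0.01 | 1.162 | 2.390 | 88.1% | 5.9% |
| 6 | 0.02 | 1.323 | 2.478 | 85.7% | 6.9% |
| 6 | 0.05 | 1.808 | 2.725 | 78.6% | 9.8% |

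**Step 4: simulation.** Controls are independent; each intervention value is a class effect plus individual error. The t-test's type I error was 5.7–6.1%, 6.2–6.9% and 7.4–9.7% at ICC 0.01, 0.02 and 0.05, within a few tenths of a point of the closed form. A class-level test (mean of class means against the control mean, Satterthwaite degrees of freedom) had power of 84–87%, 80–86% and 71–82%, and about 87–89% at ICC 0. That last figure is the price of estimating the intervention arm's variance from 6 to 12 class means, and is not due to correlation.

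**Step 5: offset from stratification.** Randomising within site makes an unadjusted t-test slightly conservative for variation shared by both arms. In a simulation at class ICC 0.05, adding a site effect of 3% of the variance moved type I error from 7.9% to 7.3% (ten classes of 10) and from 9.0% to 8.9% (seven of 15). The offset is small.

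**The case against.** The strongest reply is that the inflation is conditional. Individuals are randomised, so if hula and class membership change nobody's outcome, assignment is exchangeable within site and no class-induced inflation arises. Inflation requires classes to differ in effect around an average of zero and to be regarded as a sample of possible classes. For the average effect over just these classes and teachers, the t-test is not inflated in this way. This stands, and the point is worded accordingly. The trial's aim is nevertheless to establish whether the programme works, and the Discussion expects it to be adopted in other communities, so inference beyond these classes is the natural reading.

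The ICC is also unknown. At 0.01 the design effect alone costs only about one to two points of power. Part of the lower class-level power comes from its degrees of freedom. Both limits stand, which is why the two sets of power figures are kept apart.

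Three stronger readings are tempting:
- A reader might divide 103 completers by 20, arrive at five classes, and infer power near 66% and type I error near 10.6% at ICC 0.05. Five classes would mean 125/5 = 25 enrolled in each, above the stated maximum of about 20. Six is already the edge, and the minimum cohort of 20 per site per year points towards more, smaller classes.
- A reader might infer that the p-values are certainly too small. No document gives an ICC, so only the direction under a positive ICC can be claimed.
- A reader might infer one teacher per class. The text says only that lessons are led by a kumu hula. If one leads several classes, the relevant cluster may be larger.

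Finally, the choice of random effects and degrees of freedom is commonly left to an analysis plan. That is true of the remedy's detail. It does not cover a primary test and a power figure already stated on an independence assumption.

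**Conclusion.** The concern holds in conditional form. The t-test and the power calculation ignore grouping that exists in one arm by design. Given a positive within-class correlation and inference beyond these classes, the standard error is too small and the unqualified 90% is optimistic.

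The size is modest at an ICC of 0.01 to 0.02: type I error of roughly 6–7% and design-effect power of 86–89%. It becomes material at 0.05, where type I error is 7.4–9.7%, design-effect power 79–85%, and power of a class-level test 71–82%. These figures rest on assumed ICCs, 6 to 12 roughly equal classes, and the plan's own difference, SD and completer count. The FRS comparison uses the same test and shares the type I error issue; its power claim is not assessed here. This should be changed before analysis, but it does not undermine the design.

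**What to change.** - **Primary analysis of SBP and FRS:** replace the independent t-test with a partially nested model. Include a random effect for hula class (the site-cohort) in the intervention arm only, treat each control as their own unit, fit site as a fixed effect, and use Satterthwaite or Kenward-Roger degrees of freedom.
- **Reporting:** give the estimated within-class ICC with the result.
- **Power section:** replace the unqualified 90% for SBP with a range over ICC 0 to 0.05, stating the assumed number of classes.
- **Data:** hold each intervention participant's class, and preferably its kumu hula, in the analysis dataset. The Fidelity checks section already tracks attendance, so this adds little work.

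The cost is slightly wider intervals and a less favourable stated power. Enrolment, recruitment and delivery do not change.

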#### Wait-list control arm

After completing the 3-h HTN self-management course, participants randomized to the wait-list control arm must wait until they finish the 6-month data collection before they begin the *Ola Hou* program. In the meantime, they will be instructed to continue their usual medical care, but they will be neither encouraged nor restricted from participating in any other activity or intervention program while they wait.

#### Retention and incentive plan

All participants will receive a gift card incentive equivalent to $25 at each data collection visit, with total incentives of $100 for completing all 4 visits. For the wait-list control arm, the fourth payment will be an incentive to start the *Ola Hou* program at month 12. This strategy will ensure that all participants receive the same dollar amount of incentives, thereby avoiding any perception of unfairness – an important consideration in close-knit Native Hawaiian communities. Intervention participants will also receive an ambulatory upper-arm band BP device (valued at $40) to monitor their progress, which they can keep after the study is completed. Wait-list control participants will receive the same device when they begin the intervention. Reminder calls or emails will be made to both intervention and control participants 1 week before each data collection visit, and follow-up calls or emails will be made to allow participants who miss a data collection visit to reschedule. Participants who miss a visit and do not reschedule will be considered dropouts, and study staff will attempt to re-engage them. In our pilot study, these retention strategies successfully retained 87% of participants over a 3-month period. They should be similarly effective over the 12-month period required by the ongoing study [42].

#### Fidelity checks and data safety monitoring

To ensure the implementation fidelity of the hula intervention, research staff will intermittently visit hula classes and use a behavioral checklist to record the degree to which *kumu hula* and community peer educators follow standardized protocols. Booster training will be given as needed based on these checks. Participants will be tracked to record the number of hula and heart health classes they attend. In addition, research staff will assemble a data safety monitoring board (DSMB) composed of experts in cardiology, biostatistics, and clinical trials at study initiation who are independent from the investigators and sponsors and who will meet at least annually and as needed (e.g., review adverse events if any). The board will be responsible for reviewing trial data on an ongoing basis to ensure the safety of study participants.

#### Data management and data quality assurance

We will establish survey and data entry forms and a study databases using the research electronic data capture system (or REDCap), which allows secure and easy multi-site online access, mid-study modifications, and easy data tracking. REDCap is well-suited for CBPR that includes investigators working from different community sites. The staff of the Biostatistics and Data Management Core at the University of Hawai‘i will develop data collection instruments and a code with proper branching logic and stop actions. Participants’ data will be entered by study staff at each participating community site. A database manager will monitor data submitted online on an ongoing basis for quality control purpose and communicate with study staff to resolve any online database access and data entry issues in real-time. The REDCap database will be password protected and include the necessary encryption program to ensure data security with access only by trained research staff. All hardcopies of the participants questionnaires/surveys and lipid data will be kept in a locked, secure file cabinet in a locked room at the respective partnering community site, which will be accessible only to trained research staff. All research staff, both community and academic, will complete human subject in research training.

#### Protections against risk

One of the protection procedures for the participants is to obtain written approval by their personal physician before enrolling in the study to ensure they can participate in moderate physical activity safely. Having this approval will ensure they are also seen by their physician and that the physician is aware of participation in this study, providing the opportunity for a medical evaluation of his/her HTN (important for those who have not seen their physician within the past 6-months). A protocol will be established in the event that a participant’s blood pressure exceeds a safe level, systolic blood pressure > 180 mmHg or diastolic blood pressure > 110 mmHg, either during an assessment or during self-monitoring while in hula lesson. If BP exceeds the above cut off points, participants will wait 5 min and will be measured again. If BP is still elevated, they will be asked to go home and see their doctor as soon as possible. The participant will then be allowed to re-enter the study when cleared by their primary physician and no longer symptomatic; provided that this is done within 2 weeks. All adverse events will be immediately reported to the Principal Investigator and the DSMB for review and follow-up.

Trainings will be held for kumu hula and community peer educators, conducted by a clinician, to teach the symptoms and signs of physical distress, such as headache or blurred vision, confusion, chest pain, shortness of breath, dehydration, and edema. They will be taught how to handle these issues and when medical or emergency services are required. In the rare case that the intervention or data collection causes psychological distress, the Principle Investigator, who is a licensed clinical psychologist, will be consulted. He will meet with the participant to debrief and to determine if a referral to another mental health professional is necessary for further follow-up.

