For all follow-up assessments, the same measures administered at baseline will be re-administered, with the exception of the sociodemographic measures, along with the mediator measures. At each visit, these measures will require 15 to 35 min to complete. For participants randomized to the intervention arm, follow-up data collection will happen at 3 months, 6 months, and 12 months. Collecting data at 3 months will allow us to compare the effects of the previously tested 3-month component against its effects in the ongoing RCT, while the 6-month follow-up will assess the effects of the add-on component intended to guide behavior change. The 12-month follow-up will assess post-intervention maintenance of SBP control. Participants in the wait-list control condition will contribute follow-up data only at 3 and 6 months. For control participants, the 3-month follow-up was designed to reduce attrition by keeping them engaged and providing an additional incentive to remain in the study. The efficacy of the hula intervention will be assessed by comparing baseline, 3-month, and 6-month data between intervention and control participants.

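### As worded, the safety rule for very high blood pressure makes return to the whole study, not just to hula, depend on clearance within 2 weeks, and so could stop later outcome visits (minor)

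*Protocol article*

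**What the plan says.** Protections against risk sets the trigger at "systolic blood pressure > 180 mmHg or diastolic blood pressure > 110 mmHg, either during an assessment or during self-monitoring while in hula lesson". On a first high reading, "participants will wait 5 min and will be measured again". If the pressure is still high, the participant is sent home to see a doctor and is then "allowed to re-enter the study when cleared by their primary physician and no longer symptomatic; provided that this is done within 2 weeks".

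Four other places bear on what this means for the data:

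- **Wait-list control arm:** these participants "must wait until they finish the 6-month data collection before they begin the" hula programme.
- **Baseline and follow-up assessments:** "Participants in the wait-list control condition will contribute follow-up data only at 3 and 6 months".
- **Retention and incentive plan:** "Participants who miss a visit and do not reschedule will be considered dropouts, and study staff will attempt to re-engage them".
- **Statistical analysis:** the analysis is by intention to treat, and "Missing values for SBP and FRS at follow-up visits will be imputed by carrying forward baseline observations". A complete-case analysis is the sensitivity analysis.

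SBP is a primary outcome (Study design). It is also an input to the Framingham Risk Score (FRS), the other primary outcome (Baseline and follow-up assessments).

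**The concern.** Stopping exercise after a very high reading protects the participant. Cancelling a later scheduled blood pressure measurement does not. The rule draws no line between the two: what the participant is let back into is the study, and an assessment can trigger the rule as well as a lesson. A site worker who follows the sentence would have reason not to invite an uncleared participant to the next visit.

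The values lost this way would be related to blood pressure. They could also be lost unevenly, because only the intervention arm has lessons before month 6. Intention to treat governs how people are analysed, not whether their outcomes are collected. The planned handling then gives such a person a change of exactly 0 (baseline carried forward) or leaves them out (complete case).

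**Working it through.** **1. Which values could be lost.** Taking the sentence literally for a participant not cleared within 2 weeks:

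| Trigger | Arm | Later values lost before month 6 ends |
|---|---|---|
| Baseline assessment | either | 3 and 6 months; allocation is still concealed from participants and site staff (Randomization), so the trigger should not differ by arm |
| Lesson, months 1-3 | intervention only | 3 and 6 months |
| Month-3 assessment | either | 6 months; month-3 pressure has already been read |
| Lesson, months 4-6 | intervention only | 6 months |
| Month-6 assessment | either | no SBP value in the randomised comparison |

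The 12-month value, collected in the intervention arm only, could be lost after any of these. For wait-list participants, the loss that could relate to arm is therefore mainly the 6-month value after a month-3 trigger.

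**2. Whether another section repairs it.** The retention rule deals with people who miss a visit without rescheduling, not with people who are not let back in. No section says that outcome visits continue after the 2-week limit.

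**3. The plan's own figure.** Power analysis and sample size gives a difference of 7.5 mmHg, SD 16.5, 103 completers per arm and 90% power. The standard error (SE) is 16.5 × √(2/103) = 2.30, and 7.5/2.30 = 3.26. At two-sided 0.05, power is Φ(3.26 − 1.96) = 0.90, so the figure is reproduced. With all 125 per arm, SE = 16.5 × √(2/125) = 2.09.

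**4. Possible size of the shift.** The documents give no event, confirmation or clearance rates, so these inputs are assumptions:

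- p = fraction of one arm removed: 1%, 5% or 10% (about 1 to 12 of 125).
- g = mean change in removed people minus mean change in kept people: 0, 8.25 or 16.5 mmHg (0, 0.5 or 1 SD).
- m = true mean change in the arm: −7.6 in controls (pilot, 3 months). In the intervention arm it is −7.6 with no effect, or −7.6 − 7.5 = −15.1 with the planned effect.

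The kept mean is k = m − p·g and the removed mean is r = k + g. Carrying baseline forward gives an arm mean of (1 − p)·k, a shift of −p·r. Complete case gives k, a shift of −p·g.

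Carried-forward shift, no true effect, intervention arm only (positive is away from hula):

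| p | g = 0 | g = 8.25 | g = 16.5 |
|---|---|---|---|
| 1% | +0.08 | −0.01 | −0.09 |
| 5% | +0.38 | −0.01 | −0.40 |
| 10% | +0.76 | +0.02 | −0.73 |

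Example at 10%, g = 16.5: r = −7.6 + 0.9 × 16.5 = 7.25, so the shift is −0.1 × 7.25 = −0.73. The sign changes at g = 7.6/(1 − p), about 8. Removal from the control arm only gives the same sizes with opposite signs. Equal removal in both arms gives 0.

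Carried-forward estimate, true effect −7.5:

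| Removed from | p | g = 0 | g = 8.25 | g = 16.5 |
|---|---|---|---|---|
| Intervention | 5% | −6.74 | −7.14 | −7.53 |
| Intervention | 10% | −5.99 | −6.73 | −7.48 |
| Control | 5% | −7.88 | −7.49 | −7.10 |
| Control | 10% | −8.26 | −7.52 | −6.77 |

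The largest shift here is 0.1 × 15.1 = 1.51. Complete case shifts by at most 0.1 × 16.5 = 1.65.

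If referral made later pressure better in removed people (g = −8.25), intervention-arm removal under the planned effect gives larger dilution. At 5%, r = −15.1 − 0.95 × 8.25 = −22.94, a shift of +1.15. At 10%, r = −15.1 − 0.9 × 8.25 = −22.53, a shift of +2.25.

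**5. A simulation of the month-3 SBP trigger alone.** Assumptions: baseline drawn around 146 (SD 8 to 16, values below 140 moved above it), change SD 16.5, control change 0 or −7.6, true difference −7.5, correlation 0.6 between the 3- and 6-month changes, and half or all of those above 180 not cleared. Removal was about 0.6% to 7% of controls and 0.2% to 4% of the intervention arm. The 6-month difference moved from −7.5 to between −7.4 and −6.8 (carried forward) or between −7.4 and −7.0 (complete case).

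**The case against.** The strongest answer is that the authors meant a pause from exercise. The section opens with physician approval for moderate activity, ends with training hula teachers to recognise distress, and announces a procedure still to be set up, so the full protocol may be clearer. It never says that anyone is withdrawn or that visits stop. This stands as a reason for caution about intent. It does not settle the wording, because the rule names assessments and therefore reaches people with no hula to pause.

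Second, the plan also includes linear mixed models on all visits. Where the trigger is a recorded assessment reading, such a model can use it. However, these models are planned for examining maintenance, and a reading taken in a lesson is not among the planned outcome data.

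Third, SBP is only one cause. DBP above 110 alone triggers the rule, and return also depends on symptoms and on reaching a physician in time. This is correct: the missing data are related to blood pressure rather than determined by SBP.

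Fourth, 20% attrition is already allowed for, and the extra loss would be small. That bears on the severity, but this loss can be avoided.

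**Conclusion.** The wording is too broad and should be narrowed. Severity is minor. Followed literally, the rule creates avoidable missing outcomes that are related to blood pressure and may differ by arm. Neither baseline carried forward nor complete case repairs that.

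The likely effect is small, with no known direction. In the carried-forward analysis it is about 0 to 1.5 mmHg for 1% to 10% removal from one arm and g between 0 and 16.5. It exceeds 1.5 only if 10% are removed and those people would have done better than the rest. All the removal rates and values of g are assumptions.

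A reader might infer more than the documents support:

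- **That the trial will withdraw these participants.** No section says so, and a pause may be what was meant.
- **That the intervention arm will lose more people, or that the bias favours hula.** Lessons add occasions to trigger the rule, but an effective programme would lower the number of high readings. The frequency of blood pressure checks in lessons is not given.
- **That the SBP result is seriously threatened.** The shifts are small beside the planned effect, and most are well below one standard error.

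**What to change.** In Protections against risk, apply the physician clearance and the 2-week condition to hula attendance only. Leave the thresholds, the repeat reading and the referral to a doctor unchanged. Add that every randomised participant, cleared or not, is still invited to the scheduled 3-month, 6-month and (intervention arm) 12-month assessments and is analysed in the assigned arm.

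The cost is one or two sentences. No visits are added, because these assessments are already scheduled.
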